#### Solution

2.10.3

If the participant does not appear as planned during the follow-up period, the researcher shall know the reason as much as possible, record the reason on the case report form (CRF), contact the participant as much as possible to ask the participant to conduct a final visit, record the last medication time, try to complete the effectiveness and safety inspection when withdrawing from the study as specified in the scheme, and complete the safety follow-up period. AE and outcomes were fully recorded. According to the actual situation of the participants, researchers can suggest or provide new or alternative treatment methods to the participants.

If the participant is asking for termination of the study, researchers will retain the data and must follow-up in the specific follow-up steps specified in the study. If the participant refuses to visit further, he or she should continue to track his or her survival status unless the participant refuses to disclose further information or is contacted. In this case, no further research evaluations should be conducted, and no further information should be collected. The study sponsor may retain and continue to use all the information before the withdrawal of the participant's informed consent, unless the participant requests that the collected information be withdrawn.

### Data collection

2.11

According to the original observation record of the study, the researcher will fill in the CRF in time, complete, correct, and check it. After checking, the data manager will input the original case report form into the online database repeated, and the database is password-protected. After importing the collected patient data into the database, the data administrator and the main researcher will perform a secondary check on the data, correct all the errors, and save them properly. When the experimental data are collected, the person leading the data analysis will analyze the data.

### Sample size estimate

2.12

The RCT is an advantage test that uses an appropriate formula to estimate the sample size. Based on the results of our preliminary observational study and expert advice, we assume a significant level of α = 0.05, test efficacy (1-β) = 80%, and a pooled standard deviation of 9.59. Considering 10% dropout rate, the total sample size is expected to be 256 (128 of each carcinoma type, 64 in each group).

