#### Primary endpoint

2.8.1

The primary endpoint is PFS, the time from randomization to disease progression (Evaluation of tumor progression about RECIST 1.1) or death.

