### Statistical analysis

2.13

Analysis for primary endpoint PFS and secondary endpoint OS: the median of PFS and OS in each group was counted. Survival curves were plotted using Log-Rank test and Kaplan–Meier survival analysis.

Analysis for Symptom Improvement Assessment: behavioral status scores before and after chemotherapy (KPS), repeated measure's analysis of variance before and after treatment in the group; TCM symptom scores before and after chemotherapy (MDASI-TCM), paired *t* test before and after treatment in the group. The *t* test was used for comparison between groups.

All these statistical analyses were performed with SPSS 23.0 (SPSS Inc, Chicago, IL). A 2-tailed *P* value <.05 was considered statistically significant.

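### The sample size rests on a standard deviation for comparing means, so the stated 80% power is not a property of the primary log-rank analysis of PFS

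*Protocol article*

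**What the plan says.** Section 2.8.1 (Primary endpoint): "The primary endpoint is PFS, the time from randomization to disease progression" or death. This is a time-to-event outcome.

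Section 2.13 (Statistical analysis), for PFS and overall survival: "Survival curves were plotted using Log-Rank test and Kaplan–Meier survival analysis". Significance is two-tailed: a P "value <.05 was considered statistically significant". In that section, methods for means (t tests, repeated-measures analysis of variance) appear only for the KPS and symptom scores.

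Section 2.12 (Sample size estimate) lists four inputs:
- significance level: "we assume a significant level of α = 0.05"
- power: "test efficacy (1-β) = 80" per cent
- spread and dropout, with the result: "and a pooled standard deviation of 9.59. Considering 10% dropout rate, the total sample size is expected to be 256"

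The 256 patients are 128 per carcinoma type, 64 per arm within each type.

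**The concern.** A standard deviation does not enter the power of a log-rank test. That power is set by the number of events and the HR, and section 2.12 gives neither. The calculation it describes therefore suits a different kind of outcome from the one the trial is meant to decide.

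The stated power is what lets a reader interpret a null result. As written, a non-significant log-rank test on PFS would be read against an 80% figure that was not computed for it. Because the size is given in patients only, section 2.12 also does not show when enough PFS information has accrued for the final analysis.

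**Working it through.** **1. Can the plan's figure be reproduced?** Not from the stated inputs, because the difference to detect is missing. It can only be back-solved.

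Inputs from section 2.12: SD 9.59, alpha 0.05, power 80%, dropout 10%, 64 per arm. The two-sided test comes from section 2.13.

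Formula for two means: n per arm = 2 × (1.960 + 0.842)² × SD² / difference².

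- Back-solving: 64 × 0.9 = 57.6 evaluable per arm, which gives a difference of 5.01.
- Forward with an assumed difference of 5: n = 57.7, so 58. Inflating by multiplication, 58 × 1.1 = 63.8, so 64. Inflating by division, 58 / 0.9 = 64.4, so 65.
- A second match exists: one-sided with an assumed difference of 4.5 needs 57, and 57 / 0.9 = 63.3, so 64.

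The stated size is thus consistent with a two-sided comparison of means with a difference of about 5, run within one carcinoma type. With one free parameter, this is consistency and not proof.

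**2. What would the same patients give for a log-rank test on PFS?** The article gives no HR, so the HRs below are assumptions. Allocation is 1:1 (section 2.6) and alpha is two-sided 0.05. Schoenfeld's formulas, with d events:

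- HR detectable with 80% power = exp(−2 × 2.802 / √d)
- power = Φ(√d / 2 × |ln HR| − 1.960)

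Two event counts are used for each level of analysis: everyone left after 10% dropout has an event (128 × 0.9 ≈ 115; 256 × 0.9 ≈ 230), or every randomised patient does (128; 256).

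| Level | Events | HR for 80% power | Power at HR 0.60 | Power at HR 0.70 | Power at HR 0.75 |
|---|---|---|---|---|---|
| One type | 115 | 0.593 | 78% | 48% | 34% |
| One type | 128 | 0.609 | 82% | 52% | 37% |
| Pooled | 230 | 0.691 | 97% | 77% | 59% |
| Pooled | 256 | 0.705 | 98% | 81% | 63% |

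Worked example, d = 115 and HR 0.70: √115 / 2 = 5.362; 5.362 × 0.357 = 1.913; 1.913 − 1.960 = −0.047; Φ(−0.047) = 0.48.

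The events needed for 80% power are 121 at HR 0.60, 247 at HR 0.70 and 380 at HR 0.75.

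**3. Fewer events.** If, as an assumption, 80% of evaluable patients have an event, d is 0.8 × 115 = 92 in one type and 0.8 × 230 = 184 pooled. Power at HR 0.70 is then 40% and 68%.

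No row of this working uses the SD of 9.59, and none can be picked out as the plan's own, because the plan fixes neither the HR nor the level of analysis.

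**The case against.** The strongest defence is that a journal article condenses the full protocol, which may hold the PFS assumptions. That would answer an article silent on its basis. This one states a basis, and it does not fit the primary test. Nor does it help to suppose that 9.59 is the SD of PFS time: the calculation would still compare means, ignore censoring and lack its difference.

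Several stronger readings are tempting, and the article does not support them.

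- A reader might infer that the trial is underpowered for PFS. No target HR is given, so this is not shown. At HR 0.60 power is about 78 to 82% in one type and 97 to 98% pooled, and pooled power at HR 0.70 is close to 80%.
- A reader might see section 2.13 as pooling the carcinoma types against a per-type calculation in section 2.12. Section 2.13 speaks only of a median for each group, and section 2.12 uses the same term for the arms within one type. The level of analysis is unstated, not contradictory.
- A reader might assign 9.59 to a KPS or symptom score, since only those are analysed as means. Section 2.12 names no outcome or unit.
- A reader might treat 115 and 230 events as ceilings. Patients can progress or die before dropping out, and section 2.10.3 continues survival tracking after withdrawal. The ceilings are 128 and 256.
- A reader might call this an arithmetic error. No stated sum is shown to be wrong. The fault is a mismatch between the sample-size basis and the primary endpoint.

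**Conclusion.** The point holds in a limited form. The 80% power in section 2.12 is not a property of the primary log-rank analysis, whatever 9.59 measures, and the article leaves PFS power undetermined.

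The practical size depends on a choice that the article leaves open. Moving from one carcinoma type to the pooled comparison moves the HR detectable with 80% power from about 0.59–0.61 to about 0.69–0.70, and power at HR 0.75 from about 34–37% to about 59–63%. These figures rest on assumed HRs, proportional hazards, 1:1 allocation, two-sided 0.05, and an event in all evaluable or all randomised patients. Fewer events would lower every power. The difference of about 5 is back-solved and should not be treated as the plan's assumption.

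**What to change.** Keep 256 patients and restate section 2.12 for the log-rank test on PFS:

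1. Give the assumed HR or the median PFS in each arm, with its source, and the expected number of events.
2. State the event count at which the final PFS analysis is run.
3. Say whether the power applies within each carcinoma type or to both types pooled.
4. Replace the 80% with the power, or the detectable HR, that this design delivers at that level.
5. Name the outcome, unit and difference that 9.59 belongs to, and do not present that calculation as the power for PFS. The sponsor must supply these; they should not be filled in from the back-calculation.

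The cost is the rewording of one section, with no extra patients. The stated power may become less favourable.

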### Statistical analysis

2.13

Analysis for primary endpoint PFS and secondary endpoint OS: the median of PFS and OS in each group was counted. Survival curves were plotted using Log-Rank test and Kaplan–Meier survival analysis.

Analysis for Symptom Improvement Assessment: behavioral status scores before and after chemotherapy (KPS), repeated measure's analysis of variance before and after treatment in the group; TCM symptom scores before and after chemotherapy (MDASI-TCM), paired *t* test before and after treatment in the group. The *t* test was used for comparison between groups.

All these statistical analyses were performed with SPSS 23.0 (SPSS Inc, Chicago, IL). A 2-tailed *P* value <.05 was considered statistically significant.

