## Introduction

1

Gastric carcinoma (GC) is the fifth malignancy and the third cause of cancer death worldwide, and colorectal carcinoma (CRC) is the third most common fatal cancer worldwide.^[1,2]^ The curative treatment for non-early GC and CRC is mainly surgical, and the treatment for advanced GC and CRC is a multimodal treatment model based on chemotherapy. Due to the several phase III studies showing the treatment benefits of neoadjuvant and adjuvant chemotherapy protocols, there have been major advances in the multimodal treatment of GC and CRC.^[3–5]^ Although the total effective rate of first-line and second-line chemotherapy is better than before, the prognosis of GC and CRC still needs to be improved.

Maintenance therapy refers to the mode that patients with advanced cancer who have been given by drug treatment and have their condition under control will stop the original treatment plan and switch to other plans for the next treatment until the disease progresses. In some studies on maintenance therapy for GC, patients without progression after firstline chemotherapy that include docetaxel, cisplatin and XELOX were randomly assigned to receive capecitabine maintenance. The results showed that the median progression-free survival (PFS) and median overall survival time (OS) of the patients receiving maintenance therapy were significantly better than that of the group without maintenance therapy, and grade 3/4 adverse events (AEs) and hematological toxicity were less common during maintenance therapy.^[6,7]^ The same result has also been found in GC studies where the targeted drug trastuzumab was selected as maintenance therapy.^[8]^ These studies suggest that maintenance therapy may benefit patients with advanced GC after chemotherapy, but more research is needed in this regard.

The maintenance therapy of advanced CRC is more mature than that of GC. During the past decade, capecitabine or capecitabine combined with bevacizumab has been repeatedly used in maintenance therapy after first-line chemotherapy studies for advanced CRC, and the results showed that the PFS and OS of the maintenance group were improved compared with the control group.^[9–11]^ The evidence shows that the use of fluorouracil or targeted drugs in the maintenance therapy of advanced CRC can benefit the survival of patients, which preliminarily proves that the maintenance model is feasible in the treatment of patients with advanced CRC.

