### Study design

2.1

This study is an open, single-center, randomized controlled trial (RCT), wherein 256 patients with stage III or IV GC and CRC (128 patients of each carcinoma type) who met the inclusion criteria will be randomly assigned to 2 groups, receiving S-1 or S-1 combined with XSLJZD for 5 years. The flowchart of the study is presented in Figure 1.

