#### Secondary endpoints

2.8.2

The secondary endpoint is overall survival (OS) and Quality of Life Assessment (QOLA). OS is defined as the time from randomization to death for any reason. The last follow-up time is usually calculated as the time of death for the participants who have lost the visit before death (Additional file 1; Additional file 2; Additional file 3; Additional file 4).

QOLA, including symptom improvement, KPS, and AE assessment before and after treatment, was performed for 1 to 3 days before each cycle of treatment, Details are as follows:symptom improvement, mainly observe the changes of common symptoms of GC and CRC (pain, diarrhea, fatigue, poor acceptance, sleep), refer to the “Guiding Principles for Clinical Research of New Chinese Medicine” in the relevant TCM symptom integral quantification table of MDASI-TCM, compared to the scores accumulated for each symptom, analyze the difference before and after treatment^[30]^; KPS, comparative analysis before and after the difference; assessment of AE (safety outcomes). Assessment and grading of AE were based on the Common Terminology Criteria for Adverse Events (CTCAE) Version 4.0,^[31]^ AEs include nausea and vomiting, granulocytopenia, thrombocytopenia, anemia, impairment of liver and kidney function, diarrhea, peripheral neuritis, stomatitis, hand-foot syndrome, and any other new symptoms or diseases related to or unrelated to intervention. SAEs refer to the events that must be hospitalized or prolonged, permanently and seriously disabled, life-threatening, or death in clinical trials. SAE will be reported to the chief researcher and the hospital ethics committee, and the experiment will be stopped within 24 hours.

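### The before-and-after comparison of KPS and MDASI-TCM has no common 'after' time, so the between-arm test can pick up a difference in PFS rather than in quality of life

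*Protocol article*

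**What the plan says.** Section 2.13 of the protocol article plans a repeated-measures analysis of variance for KPS and, for MDASI-TCM, a "paired *t* test before and after treatment in the group". The KPS analysis is also worded as before versus after treatment within each group. One further sentence assigns a t test to the between-group comparison and names no time point.

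Section 2.8.2 says that the quality-of-life assessment "was performed for 1 to 3 days before each cycle of treatment". Section 2.7 sets the cycle at 21 days and gives no number of cycles.

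The text bears on the end of treatment in these places:

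- Section 2.1 has patients "receiving S-1 or S-1 combined with XSLJZD for 5 years".
- The Introduction describes maintenance in general as patients who "switch to other plans for the next treatment until the disease progresses".
- Section 2.10.2 allows earlier withdrawal, including for drug-related toxicity, unexplained delay or poor compliance.
- Section 2.10.3 asks staff to "try to complete the effectiveness and safety inspection when withdrawing from the study".

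Table 1, the detailed schedule, is not shown.

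**The concern.** A paired t test needs one 'after' value per patient. The trial collects a series of scores, and the text does not say which one is 'after treatment'. Two literal readings are available.

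- **Last on-treatment score.** Nearly every patient has one, but its date is set by progression, toxicity or withdrawal. PFS is the primary endpoint and the one the combination is meant to lengthen. If it succeeds, combination patients are scored later on average. Where scores drift with time, that gap in timing becomes a gap in scores.
- **End of the 5 years.** The date is common to all, but few patients with stage III or IV disease will reach it. The comparison is then confined to long survivors.

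On neither reading does the between-group t test answer whether adding XSLJZD changes symptoms or performance status during maintenance. Relief of chemotherapy side effects is a main part of the rationale in the Introduction and Discussion, so this comparison will be read closely even though it is secondary.

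**Working it through.** **Inputs from the article.** Section 2.12 states "we assume a significant level of α = 0.05, test efficacy (1-β) = 80%, and a pooled standard deviation of 9.59". The scale to which this SD belongs is not named, but it is the only SD available. The same section gives 64 per arm within each carcinoma type, hence 256/2 = 128 per arm with both types together. The cycle is 21 days, or 21/30.4375 = 0.690 months. The test is two-sided at 0.05.

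**The plan's own figure.** The 256 cannot be reproduced, because no difference in means is stated. Back-solving with 58 evaluable per arm gives 9.59 × √(2/58) × (1.960 + 0.842) = 4.99 points, and 58 × 1.1 = 63.8, rounded up to 64. This is consistent with the stated size and is used below only as a yardstick.

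**Assumptions (not in the article).** Time on treatment is exponential with median 6 months (S-1) or 8 months (combination), capped at 60 months. Both arms worsen at the same rate, so XSLJZD has no effect on the score at any common time.

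**Reading 1: 'after' is the last pre-cycle score.** For treatment time t, this score falls at floor(t/0.690) × 0.690 months. The mean times are 8.3 and 11.1 months. The false difference should therefore be close to the monthly rate × 2.8 months: 1.4, 2.8 and 5.6 points at 0.5, 1 and 2 points per month. Simulation among patients with at least one post-baseline score gives 1.4, 2.9 and 5.7 points, with the combination arm worse.

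Rejection rates of the two-sample t test (nominal 5%) across those three rates of worsening:

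| Worsening | 128 per arm | 64 per arm |
|---|---|---|
| limited to 10 points | about 6% to 10% | about 6% to 8% |
| limited to 20 points | about 15% to 21% | about 10% to 12% |
| unbounded | 17%, 35%, about 50% | 11%, 19%, 28% |

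Simulation error is up to about 2 percentage points. Comparison cases:

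- Equal PFS medians: 4% to 5%.
- Scores stable over time: about 5%.
- Both arms compared at one fixed visit before cycle 5: 4% to 6%.

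The share stopping before cycle 2, with no post-baseline score, is 1 − 0.5^(0.690/6) = 7.7% and 1 − 0.5^(0.690/8) = 5.8%, averaging 6.7%.

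**Reading 2: 'after' is the 5-year end.** The share alive at 60 months is 2^(−60/median OS):

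- median 12 months: 3.1%
- median 15 months: 6.3%
- median 18 months: 9.9%
- median 24 months: 17.7%

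**The case against.** The strongest reply is that this is loose wording which a full plan would tidy up. Table 1 is not shown and could date a visit. A score taken just before one cycle is also the score after the previous one, and the withdrawal section asks for an assessment on leaving. All of that is fair. A reader might infer that the trial has no post-treatment score at all, and the visible text does not support this. What stands is narrower: section 2.13 fixes a two-point analysis beside a per-cycle schedule and refers to no dated visit.

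A reader might also infer that KPS rests on a single 'after' score. It does not have to, because a repeated-measures analysis of variance could use the per-cycle scores. The point is firmest for MDASI-TCM and for the between-group t test. It reaches KPS only through the before/after wording.

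The 5-year reading is the less likely one, since scores are collected every cycle. The description of treatment until progression is a general definition in the Introduction, not this trial's stopping rule.

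The size is also open to challenge. Unbounded worsening at 2 points per month for 60 months would be 120 points, which a 0 to 100 scale such as KPS cannot show. The bounded rows are therefore the more realistic ones for KPS, and they are much smaller.

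**Conclusion.** The point holds in a limited form. As worded, the between-arm comparison of MDASI-TCM, and of KPS if analysed the same way, has no common 'after' time and can be distorted by a difference in PFS.

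On the last-score reading, with medians of 6 versus 8 months, SD 9.59 and 128 per arm, false rejection is about 6% to 21% when worsening is limited to 10 to 20 points. It reaches about 50% only if worsening is unbounded. Two conditions are both needed: PFS must differ between arms, and scores must worsen with time. On the 5-year reading, 3% to 18% would be alive to be scored for assumed median OS of 12 to 24 months.

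A reader might conclude that the combination arm will look worse. The documents do not support that. Patients enter with disease controlled by chemotherapy. If their scores stay stable there is no bias, and if they recover the sign reverses. The article gives no PFS, OS or score trajectory to settle this.

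The change is worth making because it is cheap and the endpoint is prominent. PFS and OS are not affected.

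**What to change.** In sections 2.13 and 2.8.2:

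- Make the between-arm comparison of KPS and MDASI-TCM at one pre-specified time from randomisation. The assessment before cycle 5 is an example: 4 × 21 = 84 days, which coincides with the third 28 ± 3-day follow-up (3 × 28 = 84) if cycle 1 starts at randomisation. Equally good is a longitudinal model of all per-cycle scores that reports the arm difference at that time.
- Seek that score also from patients who have stopped study drug but remain in follow-up and have not refused further assessment.
- State how deaths before that time are handled, for example worst rank in a rank-based comparison.
- Keep last-score and end-of-treatment comparisons descriptive.
- Reconcile the statements on treatment duration, so that the text says what 'after treatment' refers to.

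The cost is a wording change plus one extra KPS and questionnaire at an existing contact for early stoppers. Under the assumed medians these are at most 1 − 0.5^(3/6) = 29% and 1 − 0.5^(3/8) = 23% of patients at three months, including any who have died. The downside is that effects appearing only after the chosen time become descriptive.
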